#### Bioethics

The first stage of the study was conducted according to the ethical principles established in the Declaration of Helsinki. The Ethics Committee of Peking Union Medical College Hospital (S-K540) approved the protocol. Written informed consent was provided by all patients enrolled in this study.

### Applying the frailty prediction model in the clinic

#### Population and inclusion and exclusion criteria

All older patients (age 65 years or more, BI scores ≥ 75 points, and estimated survival time > 3 months) who were hospitalized for minimum of 4 days in the wards of Peking Union Medical College Hospital, will be screened by a research assistant using the frailty prediction model. The other inclusion criteria are the same as in the first stage of the study. In the second stage, we will also exclude patients who were included in model development during the first stage.

#### Feasibility of recruitment and sample size

In the second stage, a previous study suggested that the relative risk of readmission is 1.9 among the malnourished older patients compared with the robust [60], and the hospital readmission rate among healthy older people with nutritional risk is 17 %. Taking into account an expected refusal rate of 20 %, we aim to include two groups of 266 patients, to be reached in approximately 6 months.

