**Methods:**

The proposed study includes two stages. In the first stage, we aim to develop a prediction model of frailty among older inpatients with nutritional risk. Study data were collected from a population-based aging cohort study in China. A prospective cohort study design will be used in the second stage of the study. We will recruit 266 older inpatients (age 65 years or older) with nutritional risk, and we will apply the frailty model in the clinic to explore the predictive ability of the model in participants, assess patients’ health outcomes with implementation of the frailty model, and compare the model with existing frailty assessment tools. Patients’ health outcomes will be measured at admission and at 30-day follow-up.

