#### Population and inclusion and exclusion criteria

In the first stage of modeling, participants must meet the following criteria: having no frailty according to the FRAIL (Fatigue, Resistance, Ambulation, Illnesses, & Loss of Weight) scale (scores from 0 to 2), malnourished or at risk of malnutrition according to the Mini-Nutritional Assessment-Short Form (MNA-SF; scores range from 0 to 11), and written informed consent provided by patients enrolled in this study.

Exclusion criterion were as follows: patients with frailty at the time of enrollment; patients who are persistently unconsciousness or unable to provide informed consent for participation, or their caregivers were unable to provide effective information; patients who were initially admitted to the intensive care unit (ICU) [13]; patients with anorexia nervosa, acute pancreatitis, acute liver failure, cystic fibrosis, stem cell transplantation, severe chronic gastrointestinal diseases, acute infectious diseases or chronic wasting diseases at enrollment; and patients who were lost to follow-up or had died at the 30-day of follow-up. A total of 3027 patients were enrolled in the current study.

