#### Statistical analysis

Continuous variables are described using mean and SD or median with interquartile range in the case of a skewed distribution. Categorical variables are described as number and percentage. ANOVA will be used to examine the statistical differences in variables among different groups. We will perform bivariate analyses using the χ^2^ test or Fisher’s exact test for qualitative variables and Kruskal–Wallis test for quantitative variables. Cox proportional hazards models will be constructed to determine the association of frailty score at baseline with mortality. Multiple linear regression models will be applied to evaluate the relationship between baseline frailty score and health clinical outcomes. We will use the Kappa statistic to evaluate the consistency of the new frailty prediction model and FP. The correlation between biochemical markers and frailty will be assessed using Pearson’s correlation coefficient. All statistical analysis will be performed using Stata version 14 for Windows (Stata Corp, College Station, TX, USA). A *P* value of less than 0.05 is considered statistically significant.

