## Discussion

This project is the first to develop an early prediction model of frailty for older inpatients according to nutritional risk in a nationally representative sample of older Chinese inpatients in tertiary hospital.

In the past two decades, Fried et al. [22], Mitnitski et al. [64], Rockwood et al. [65] and other researchers [36, 66] have made great contributions to the measurement tools available for identifying frailty. These include the physical phenotype model of Fried et al. [22] and the FRAIL scale [36], the deficit accumulation models of Mitnitski [64] and Rockwood [65], which capture multimorbidity; and mixed physical and psychosocial models, such as the Tilburg Frailty Indicator [66] and Edmonton Frailty Scale [67]. However, the theoretical basis, evaluation items, evaluation methods, and applicable objects differ among these assessment tools. Additionally, none of these tools have been developed on the basis of the Asia-Pacific region, which has the largest population of older adults worldwide combined with large heterogeneity regarding population socioeconomics, provision of health care services, and ethnic diversity [58], especially among the aging Chinese population [6–8].

Many researchers have indicated that frailty is multidimensional and that its definition should comprise nutrition, cognition, mentality, ADL, and other aspects [26–30, 58]. Therefore, using this protocol, we aim to adopt findings and assessment tools from previous studies, and to develop a frailty prediction model according to nutritional risk. Early assessment to identify frailty or pre-frailty is critical in older inpatients and may help in targeting interventions to address and reduce adverse clinical outcomes and improve patient quality of life.

The limitations of this study include the older inpatients enrolled in the first stage of our study were selected from tertiary hospitals and from only one hospital in each province or municipality/city, which may limit the generalizability of our results to different settings. Additionally, the estimated sample size is not sufficiently large in the second stage of the study (*n* = 266).

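### The Stage 2 sample size is stated inconsistently (two groups of 266 against 266 in all), and its basis is a contrast and an endpoint that do not fit the study

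*Protocol article*

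**What the plan says.** The target is given in three places in the protocol article.

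- Stage 2, Feasibility of recruitment and sample size: "we aim to include two groups of 266 patients".
- Abstract, Methods: "We will recruit 266 older inpatients (age 65 years or older) with nutritional risk".
- Discussion, limitations: "the estimated sample size is not sufficiently large in the second stage of the study", with n = 266 in brackets.

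The Stage 2 sample-size section offers three inputs: "the relative risk of readmission is 1.9 among the malnourished older patients compared with the robust"; "the hospital readmission rate among healthy older people with nutritional risk is 17" per cent; and "an expected refusal rate of 20" per cent. It does not define the two groups.

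Stage 2 carries over the remaining Stage 1 inclusion criteria, which require patients to be "malnourished or at risk of malnutrition according to the Mini-Nutritional Assessment-Short Form", that is, a score of 0 to 11. The Stage 2 Procedure section repeats that range.

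Under Outcome parameters, the primary endpoint is a 30-day composite of six elements: non-elective readmission, frailty, death, ICU admission, Barthel Index decline of 10% or more, and major complications. The Stage 2 Statistical analysis section relates baseline frailty score to mortality and other outcomes, and measures agreement with the Fried phenotype by kappa.

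**The concern.** Two things look wrong. First, the section that fixes the recruitment target can be read as twice the number given in the Abstract and Discussion.

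Second, the rationale describes a different study. It needs a robust or well-nourished reference group, which the eligibility criteria exclude. It pairs the ratio with a rate taken from people who already have nutritional risk. It also concerns readmission alone, with no rate or effect given for the composite.

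The allowance is misplaced as well. Refusal reduces the number who consent among those approached; it does not deplete patients already included. Stage 1 allows 10–20% for loss to follow-up, but the Stage 2 section mentions no such loss, although the endpoint is read at 30 days.

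At stake is whether staff know when recruitment is complete, and whether the article supports any statement about what Stage 2 can detect or estimate.

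**Working it through.** **Inputs from the article.** Relative risk 1.9; readmission rate 17%; refusal 20%; general significance level ("value of less than 0.05 is considered statistically significant"). Power, sidedness, test and allocation are not stated in the sample-size section. I assume two-sided 5%, 80% or 90% power, and 1:1 allocation.

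**Two readings of the rates.** If 17% is the reference rate, the other is 0.17 × 1.9 = 0.323. If 17% is the exposed rate, which its description allows, the other is 0.17 / 1.9 = 0.0895 (8.9%).

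**Sample size.** The pooled two-proportion formula per group is

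n = [z_α √(2p̄q̄) + z_β √(p1q1 + p2q2)]² / (p1 − p2)²

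- 17% v 32.3%, 80% power: p̄ = 0.2465; [1.96√(2 × 0.2465 × 0.7535) + 0.8416√(0.1411 + 0.2187)]² / 0.153² = 123.4, so 124 per group. 124 / 0.8 = 155 per group, 310 in total.
- 17% v 32.3%, 90% power: 165 per group. 165 / 0.8 = 206.25, so 207 per group, 414 in total.
- 8.9% v 17%, 80% power: 273 per group. 273 / 0.8 = 341.25, so 342 per group, 684 in total.

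**Trying to reproduce 266 or 532.** I also used unpooled, arcsine and continuity-corrected versions, and took the allowance either as n / 0.8 or as n × 1.2. With two-sided 5%, 1:1 allocation and the allowance included, the totals are:

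| Rates | 80% power | 90% power |
|---|---|---|
| 17% v 32.3% | 291–343 | 389–445 |
| 8.9% v 17% | 644–743 | 860–973 |

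Neither 266 nor 532 is within 3% of any of these. Nor does 266 match a per-group figure.

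Other choices do come close:

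- 17% v 32.3%, one-sided, 80% power, continuity correction, × 1.2: 264 in total.
- 17% v 32.3%, one-sided, 90% power, no allowance: 264–270 in total (266 exactly with the arcsine version).
- 17% v 32.3%, two-sided, 95% power, continuity correction: 272 per group (n / 0.8) or 261 per group (× 1.2).
- 17% v 32.3%, two-sided, 90% power, 1:3 allocation, n / 0.8: 534 in total.
- 8.9% v 17%, one-sided, 80% power, n / 0.8: 264–269 per group.
- 8.9% v 17%, two-sided, 80% power, no allowance: 268–273 per group.

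**Power by reading.** Two-sided 5%, balanced groups, pooled test. The 20% loss is an assumption, at the upper end of the Stage 1 allowance.

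| Rates | 266 in total, all evaluable | 266 in total, 20% lost | 532, all evaluable | 532, 20% lost |
|---|---|---|---|---|
| 17% v 32.3% | 83% | 74% | 98.5% | 96% |
| 8.9% v 17% | 50% | about 42% | 79% | about 70% |

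Unequal groups lower these figures. If only 20% of 266 fell in the higher-risk group (my assumption; the article gives no split), power at 17% v 32.3% would be about 68%.

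**Precision for the composite.** The article gives no event rate, so I use the worst case, p = 0.5. The 95% half-width for an overall proportion is 1.96 × 0.5 / √n.

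- n = 266: 0.98 / 16.31 = 0.060, about 6 percentage points.
- n = 0.8 × 266 = 212.8: 0.98 / 14.59 = 0.067, about 7 percentage points.

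**The case against.** The Abstract and Discussion agree, so the odd phrase in the sample-size section may simply mean two groups totalling 266. That is plausible, and it makes 266 in total the likelier intention. The sentence does not say so, however, and it is the one that sets the target.

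A reader might go further and infer that neither 266 nor 532 can follow from the stated inputs. The article does not support that. Power, sidedness, test and allocation are not given, and several combinations of those choices land on or near 266 in total, or near 266 per group. Such matches, found after the fact, do not confirm the figure, but they rule out the stronger claim. In a condensed article, leaving out those settings is not itself a fault.

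A reader might also infer that 266 gives about 83% power, or that it is plainly too small. Either depends on which way the 17% is read and on how the cohort divides, and neither is settled.

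On the contrast, robust could mean a FRAIL score of 0, and such patients are eligible. That is a different axis from malnutrition, so it does not rescue a ratio described as malnourished against robust.

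Finally, Stage 2 is an observational cohort with short follow-up, and the Discussion openly concedes that the sample is not large enough. The disclosure deserves credit, and nothing obliges Stage 2 to adopt the Stage 1 loss rate. But the concession neither reconciles the two numbers nor repairs the rationale.

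**Conclusion.** The point holds in this form. The Stage 2 target is inconsistent, by a factor of two on the literal reading. Its stated basis uses a comparator that the eligibility criteria exclude, a rate that does not belong to the ratio's reference group, and one of six components of the primary endpoint. The number cannot be verified from the article. It agrees with no conventional two-sided 5% calculation at 80% or 90% power with 1:1 allocation and the 20% allowance.

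The inconsistency and the mismatch rest on the text alone. The power figures rest on the assumed test settings, on balanced groups, and on which rate the 17% represents. With 266 in total they run from about 42% to 83% across the two readings, with 20% lost or none. They describe readmission, not the composite.

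**What to change.** Rewrite the Stage 2 sample-size paragraph as follows.

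1. Give one number and use it in the Abstract, the sample-size section and the Discussion: 266 in total, if the Abstract and Discussion are right.
2. Name the two groups as a contrast that exists in the cohort and will be analysed, for example model-predicted high against low risk.
3. Stop presenting the malnourished-against-robust relative risk as the justification.
4. State what 266 delivers for the composite as precision: a 95% half-width for the overall proportion of at most about 6 percentage points if all are evaluable, and about 7 if 20% are lost.
5. If a power figure is kept, label it conditional on assumed readmission rates, a two-sided 5% test and a balanced split, and give the range: 83% and 74% (all evaluable, 20% lost) for 17% v 32.3%; 50% and about 42% for 8.9% v 17%. Say that it is lower if the groups are markedly unequal.
6. Treat the 20% refusal as a screening figure, and state any loss-to-follow-up allowance separately.

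The cost is one paragraph and a less favourable stated justification. If 266 in total is confirmed, no extra patients are needed.

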#### Procedure

After obtaining participants’ informed consent, an inventory will be made of possible confounders. This includes the following: sociodemographic data (age, sex, ethnicity, marital status, education level, type of insurance), hospital admissions, medical diagnosis, living conditions, smoking, and alcohol consumption.

Anthropometric indicators will include admission to the following. (1) Standing height; in the case of bedridden patients, the formula of Chumlea will be used to estimate height [61]. (2) Weight. (3) BMI. (4) Handgrip strength in kg, measured with a hydraulic hand dynamometer (EH101; Camry, Guangdong Province, China)  [62]. Patients will be seated with forearms resting on the arms of a chair and asked to perform three maximum force trials with their dominant hand, using the second handle position. The maximum grip score among the three values will be used [63]. Nutritional risk will be measured using MNA-SF score (0–11 points ranging from “malnourished” to “at risk of malnutrition”) [10]. For frailty assessment, the Fried frailty phenotypes (FPs) [22] will be adopted as the “standard” for comparisons with the frailty model developed in the first stage of the current study. The five phenotypes of frailty that will be used include poor appetite, exhaustion, low physical activity, poor walking ability, and poor twisting ability of fingers. Participants are to be classified as non-frail, pre-frail, and frail when meeting 0, 1 or 2, and ≥ 3 criteria [43].

To determine the degree of dependency, the BI will be used to perform physical function assessment (basic ADL) among patients. Data collection will be carried out by direct observation or by asking the patient, if possible. Scores range from 0 to 100, with a higher score indicating greater independence.

Biochemical markers include serum albumin and prealbumin (colorimetry), hemoglobin and hematocrit (fluorescence and optical methods), cholesterol (enzymatic techniques), and myokines (enzyme-linked immunosorbent assay (ELISA); Shanghai Enzyme-Linked Biotechnology Co., Ltd.).

#### Outcome parameters

Health outcomes will be measured at admission and at 30-day follow-up. The composite primary endpoint includes adverse clinical outcomes within 30 days: non-elective hospital readmission after discharge (second and subsequent hospitalizations during the period analyzed), frailty, all-cause mortality (all-cause mortality recorded at 30 days, including in-hospital deaths), ICU admission, a decline in functional status of 10 % or more from admission to day 30 as measured with the BI, and major complications as a new occurrence including adjudicated diagnosis of nosocomial infection, respiratory failure, cardiovascular event (i.e., stroke, intracranial bleeding, cardiac arrest, myocardial infarction, pulmonary embolism), acute renal failure, and gastrointestinal failure (i.e., hemorrhage, intestinal perforation, acute pancreatitis) [13].

The main secondary endpoints include length of hospital stay (LoS; duration of hospitalization, number of hospitalization days), health-related quality of life as measured using the three-level EuroQol five-dimensions (EQ-5D-3 L) questionnaire; index values range from 0 to 1, with higher scores indicating better quality of life, including the self-assessment visual analogue scale (EQ-5D VAS; scores range from 0 to 100, with higher scores indicating better health status).

#### Statistical analysis

Continuous variables are described using mean and SD or median with interquartile range in the case of a skewed distribution. Categorical variables are described as number and percentage. ANOVA will be used to examine the statistical differences in variables among different groups. We will perform bivariate analyses using the χ^2^ test or Fisher’s exact test for qualitative variables and Kruskal–Wallis test for quantitative variables. Cox proportional hazards models will be constructed to determine the association of frailty score at baseline with mortality. Multiple linear regression models will be applied to evaluate the relationship between baseline frailty score and health clinical outcomes. We will use the Kappa statistic to evaluate the consistency of the new frailty prediction model and FP. The correlation between biochemical markers and frailty will be assessed using Pearson’s correlation coefficient. All statistical analysis will be performed using Stata version 14 for Windows (Stata Corp, College Station, TX, USA). A *P* value of less than 0.05 is considered statistically significant.

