## Methods

### Study design

The study includes two stages. In the first stage, we aim to develop a prediction model of frailty among older inpatients with nutritional risk. Study data were collected from a population-based aging cohort study in China. A prospective cohort study design will be used in the second stage of the study. We will apply the frailty model in the clinic to explore the predictive ability of the model in participants, assess patients’ health outcomes with implementation of the frailty model, and compare the model with existing frailty assessment tools.

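### Stage 2 declares a 30-day composite primary endpoint, but its analysis section names no analysis of that composite and does not say which frailty score is the predictor

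*Protocol article*

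**What the plan says.** All places are in the Protocol article, under Applying the frailty prediction model in the clinic unless stated.

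- **Outcome parameters:** "The composite primary endpoint includes adverse clinical outcomes within 30 days". Six component types follow: non-elective readmission, frailty, death, ICU admission, a Barthel Index decline of at least 10%, and major complications. Length of stay, EQ-5D index and EQ-5D VAS are the main secondary endpoints.
- **Statistical analysis**, the two models that relate baseline frailty to outcomes: "Cox proportional hazards models will be constructed to determine the association of frailty score at baseline with mortality" and "Multiple linear regression models will be applied to evaluate the relationship between baseline frailty score and health clinical outcomes". The second set of outcomes is not listed. Kappa is named for agreement between the new model and the Fried phenotype, and Pearson correlation for markers against frailty. The threshold is common to all: "A *P* value of less than 0.05 is considered statistically significant".
- **Feasibility of recruitment and sample size:** the inputs are a relative risk of readmission of 1.9 (malnourished versus robust), a 17% reference readmission rate and 20% refusal.
- **Procedure:** "Biochemical markers include serum albumin and prealbumin (colorimetry), hemoglobin and hematocrit (fluorescence and optical methods), cholesterol (enzymatic techniques), and myokines". The Fried phenotype is the comparison standard.
- **Study design:** Stage 2 is to explore the model's predictive ability, assess health outcomes and "compare the model with existing frailty assessment tools".

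**The concern.** Three sections point to three different deciding questions. The endpoint section points to the composite, the sample-size section to readmission by nutritional group, and the analysis section to mortality plus an open list of outcomes. A reader of the eventual report could not tell from this document which result answers the primary question.

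The predictor is equally open. The Stage 1 model's score and the Fried count are both obtained at baseline. A FRAIL score is available too, because Stage 2 takes over the Stage 1 entry criteria. Only an analysis of the model's score says anything about the model this study develops.

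The candidate contrasts can disagree. The composite might show no association while EQ-5D VAS, or one marker, gives P<0.05. The document does not say which would count.

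**Working it through.** **1. The plan's own figure, 266.** Inputs from the sample-size section: p1 = 0.17 and p2 = 1.9 × 0.17 = 0.323. Power and sidedness are not stated. For two proportions, assuming two-sided 0.05 and 80% power:

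n per group = [1.96·√(2·p̄·(1−p̄)) + 0.842·√(p1(1−p1) + p2(1−p2))]² / (p2−p1)², with p̄ = 0.2465

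= [1.96 × 0.6095 + 0.842 × 0.5998]² / 0.153² ≈ 123.4, so 124 per group and 248 in total. Allowing for 20% refusal gives 248/0.8 = 310. The 266 is not reproduced this way. Only choices that the article does not state come near it; for example, one-sided 80% power with continuity correction and a multiplier of 1.2 gives 264. How 266 arose is therefore undetermined. (The section can be read as 266 per group; the abstract and the limitations give 266 in total, which is used here.) What matters is that every input concerns readmission, and none concerns the composite.

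**2. The sections side by side.**

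| Item | Where it stands | What the Stage 2 analysis section does with it |
|---|---|---|
| 30-day composite (primary) | Outcome parameters | Not named |
| Mortality (one component) | Outcome parameters | Own Cox model |
| Other components, length of stay, EQ-5D | Outcome parameters | Presumably the unlisted outcomes, by linear regression |
| Readmission, malnourished versus robust | Sample size | Not named |
| Six marker types | Procedure | Pearson correlation with frailty |

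The composite is a yes/no outcome. Apart from the Cox model for death, the only regression offered for the frailty score is linear.

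**3. Which frailty.** The analysis section does not say which instrument gives the baseline score or the frailty correlated with markers. The endpoint section does not say which defines frailty at 30 days. Stage 1 defines its outcome by FRAIL, while Stage 2 takes the Fried phenotype as standard.

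**4. Chance of at least one P<0.05 if nothing is associated.** Test counts are inferred:

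- 9: mortality, other outcomes (as one), quality of life (as one), 6 markers.
- 14: mortality, readmission, ICU admission, Barthel decline, complications, length of stay, EQ-5D index, VAS, 6 markers.
- 15: the 14 plus 30-day frailty.

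Myokines are counted once although they are a class. For independent tests the chance is 1 − 0.95^m. For correlated tests, 400,000 draws of m equally correlated normal statistics were compared with ±1.96.

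| m | independent | corr. 0.3 | corr. 0.5 | corr. 0.7 |
|---|---|---|---|---|
| 9 | 37% | 33% | 27% | 20% |
| 14 | 51% | 44% | 35% | 25% |
| 15 | 54% | 46% | 36% | 26% |

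**The case against.** **This is a condensed article and an analysis plan may exist.** That disposes of part of the matter. Testing order, Holm or false-discovery-rate adjustment, and exploratory labels for secondary and marker analyses are commonly left to such a plan, and their absence is no finding here. It does not dispose of the conflict between the endpoint, sample-size and analysis sections, since a later plan would have to override one of them.

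**The composite may be meant among the health clinical outcomes, or be covered by the general χ² sentence.** Either is possible. Under the first reading a yes/no primary endpoint goes to linear regression as one unnamed item in a list. Under the second, neither the groups nor the outcome is stated. Neither gives it a deciding role.

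**The model score is the natural reading of the predictor.** This has weight: the Study design ties health outcomes to use of the model, and the Procedure gives the Fried phenotype a comparator role. But the analysis section does not say so.

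**Stage 2 is worded as exploratory, and the P<0.05 sentence is a general convention** that appears in almost the same words for Stage 1. So one cannot infer that every test has confirmatory standing. Endpoints are also ranked as primary and secondary. Even so, a declared primary endpoint with no named analysis remains inconsistent.

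**The global null is artificial.** The Background itself links frailty to readmission, longer stay, poorer quality of life and early death. The percentages above therefore describe a worst case, not a forecast.

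**Conclusion.** The point holds as an inconsistency between stated sections. Stage 2 has a declared primary endpoint with no named analysis, a sample size built on a contrast the analysis section does not name, and a predictor that is not identified. Under one common P<0.05, the chance of at least one false positive is about 27–36% at a correlation of 0.5 and 37–54% if the tests are independent. This rests on an inferred 9 to 15 tests, assumed correlations and no true association anywhere.

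Two stronger readings are tempting, and the documents support neither.

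- *A chance positive is likely.* The rate passes 50% only with about 14 or more independent null tests (49% at 13, 51% at 14). With the correlations tried it stays below that.
- *A chance positive will be presented as validating the model.* No section says a significant association would count as validation. The stated aim is to explore predictive ability, and the only named check against the declared standard is Kappa.

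**What to change.** In the Stage 2 Statistical analysis section:

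1. Name one primary contrast: the Stage 1 model's score at admission against occurrence of the 30-day composite, with a model for a yes/no outcome (for example logistic regression), at two-sided 0.05.
2. State that the frailty score means the model's score, with the Fried count as comparator.
3. State which instrument defines 30-day frailty within the composite, and report the result with and without that component; otherwise a frailty score is tested partly against frailty.
4. Report the mortality Cox model, the other components, length of stay, EQ-5D index and VAS, and the markers as secondary or exploratory estimates with 95% CIs.
5. State that the sample size was based on readmission, not on the composite.

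This takes a few sentences. The deciding test then has a 5% error rate. Adjusting everything instead would be expensive: Bonferroni over 14 tests gives 0.05/14 = 0.0036 per test and, assuming 133 per group (266/2), cuts power for the 17% versus 32.3% readmission contrast from 83% to 49%.

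The downside is that an isolated secondary or marker result with P<0.05 can no longer be presented as the main finding. Power for the composite remains unknown, because the article gives no event rate for it.

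### The Stage 2 primary composite is in effect yes/no, but the only adjusted model stated for clinical outcomes other than mortality is multiple linear regression, which does not fit it

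*Protocol article*

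**What the plan says.** All references are to the protocol article, in the part on applying the frailty prediction model in the clinic.

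- *Outcome parameters*: "The composite primary endpoint includes adverse clinical outcomes within 30 days: non-elective hospital readmission after discharge", followed by "frailty, all-cause mortality (all-cause mortality recorded at 30 days, including in-hospital deaths), ICU admission", then "a decline in functional status of 10 % or more from admission to day 30 as measured with the BI", and new major complications. Timing: "Health outcomes will be measured at admission and at 30-day follow-up". Length of stay, the EQ-5D-3L index and the EQ-5D VAS are the main secondary endpoints.
- *Statistical analysis* gives two outcome models. The first is for death: "Cox proportional hazards models will be constructed to determine the association of frailty score at baseline with mortality". The second is for the rest: "Multiple linear regression models will be applied to evaluate the relationship between baseline frailty score and health clinical outcomes".
- The same section lists simple tests: "We will perform bivariate analyses using the χ^2^ test or Fisher’s exact test for qualitative variables and Kruskal–Wallis test for quantitative variables". It links none of them to the composite.
- *Procedure* has possible confounders recorded, so an adjusted analysis is evidently intended.
- *Feasibility of recruitment and sample size* is built on a binary event: readmission at 17%, with a relative risk of 1.9.
- Logistic regression is named only in Stage 1 (*Statistical considerations*).

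**The concern.** The primary endpoint and the model that appears to cover it are of different types. The composite is described as adverse clinical outcomes, and the linear-regression sentence is about clinical outcomes, so the natural reading applies a model for continuous outcomes to a yes/no variable. No binary-outcome regression is named anywhere in Stage 2, and the Cox model is kept for mortality.

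Three things are at stake. The sample size is argued on a risk-ratio scale, while linear regression returns risk differences. Predicted risks, which matter for a warning tool, can be impossible values. Confidence intervals can be too narrow or too wide. In addition, if the adjusted model for the primary question is not settled in advance, it may be chosen after the outcomes are seen.

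**Working it through.** **Step 1. Type of endpoint.** Readmission, frailty, death, ICU admission and major complication are events. The Barthel Index component is a change cut at 10%. A composite of these is yes or no for each patient at day 30. Frailty and the Barthel decline are known only from the day-30 visit, so they carry no true event time. A fixed 30-day binary analysis therefore fits the design better than time to first event.

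**Step 2. Inputs.** The risk in the reference group is p0 = 0.17 (the plan). The risk in the other group is p1 = 0.17 × 1.9 = 0.323. These are readmission risks and stand in for composite risks, which the article does not give. The share of patients in the high-risk group, f, is not given for Stage 2, so a range is assumed. The nearest figure in the document is the 40% frailty incidence expected in Stage 1.

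**Step 3. Standard error of the risk difference under linear regression, two-group exposure.**

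- N × true variance = p0(1−p0)/(1−f) + p1(1−p1)/f, with p0(1−p0) = 0.1411 and p1(1−p1) = 0.2187.
- N × ordinary linear-regression variance = [(1−f) × 0.1411 + f × 0.2187] × [1/(1−f) + 1/f].
- SE ratio = √(linear-regression variance / true variance). Coverage = 2Φ(1.96 × ratio) − 1.

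For f = 0.2, the true value is 0.1764 + 1.0934 = 1.270. The linear-regression value is 0.1566 × 6.25 = 0.979. The ratio is √(0.979/1.270) = 0.878, and coverage is 2Φ(1.721) − 1 = 91.5%.

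| Assumed f | SE ratio | Coverage of nominal 95% interval |
|---|---|---|
| 0.1 | 0.840 | 90.0% |
| 0.2 | 0.878 | 91.5% |
| 0.3 | 0.917 | 92.8% |
| 0.4 | 0.958 | 93.9% |
| 0.5 | 1.000 | 95.0% |
| 0.6 | 1.044 | 95.9% |

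N cancels, so these results do not depend on whether 266 is the total or the size of each group.

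**Step 4. Continuous score.** The analysis section uses a frailty score rather than two groups, so a simulation was run with a standardised score, N = 266, and assumed event rates at the average score of 17%, 30% and 50% (1,000 runs each).

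- No association: linear regression rejected in 5.0%, 4.9% and 4.6% of runs, and logistic regression in 4.6%, 4.6% and 4.4%. The simulation error is about √(0.05 × 0.95/1000) = 0.7 percentage points, so all are compatible with 5%.
- Assumed log odds ratio of 0.7 per SD (odds ratio about 2): both models rejected in 98.7%, 99.7% and 99.9% of runs. Linear regression put 3.3%, 1.4% and 0.4% of fitted risks outside 0–1.

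**Step 5. Events for the Cox model.** Stage 2 requires an expected survival beyond three months. The document gives no 30-day mortality. Assuming 0.5–2% and reading 266 as the total (266 × 0.8 = 213 after the 20% allowance), expected deaths run from 0.005 × 213 = 1.1 to 0.02 × 266 = 5.3. Reading 266 as the size of each group (532 in all), the upper end is 0.02 × 532 = 10.6.

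**The case against.** The strongest reply is that the article never says the composite will be fitted by linear regression. The phrase about clinical outcomes is loose and also takes in length of stay and the two EQ-5D measures. Linear regression is a usual choice for EQ-5D and VAS. A reader might infer that the whole sentence is wrong, and it is not. What remains is that no other adjusted model is offered for the primary endpoint. Because the article does name a model, this is not just detail left to a fuller document.

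Four stronger readings are tempting and are not supported.

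- *The primary question has no valid analysis.* A yes/no composite is a qualitative variable, so the listed χ² or Fisher tests would give a valid unadjusted comparison between groups.
- *P values would be seriously wrong.* With no association a binary outcome has constant variance, and the simulated error rate was near 5%. The fault lies in fit, effect scale and interval width, and the interval error disappears with equal groups and reverses above 50%.
- *The score merely predicts itself.* Stage 2 carries over the Stage 1 inclusion criterion of a FRAIL score of 0–2, so frailty at day 30 is a new event and predicting it is prognosis. What stands is narrower: frailty is the outcome the score was built to predict, so it could dominate a positive composite.
- *The Cox model is the wrong model.* It is a suitable type for mortality. The problem is likely imprecision, and the size of that rests on an assumed death rate.

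**Conclusion.** The point holds in a limited form: the stated adjusted model does not match the binary primary endpoint, and the tests that would match it are neither adjusted nor assigned to it. The effect on interval coverage ranges from a loss of about 3.5 percentage points (assumed 20% high-risk) through about 1 point (40%) to none (50%). This uses readmission risks in place of composite risks and a two-group exposure. Impossible fitted risks would be few, 0.4–3.3% of patients under an assumed odds ratio of about 2 per SD. The mismatch itself rests on the text alone and needs none of these assumptions. It deserves correction because it concerns the primary endpoint and is simple to put right.

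**What to change.** In Stage 2 *Statistical analysis*:

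1. Name one primary analysis: logistic regression, or modified Poisson regression with robust standard errors, of the 30-day composite on the baseline frailty score, adjusted for the confounders listed in *Procedure*. Modified Poisson would report on the risk-ratio scale used for the sample size.
2. Use the same model for the binary components that have enough events.
3. Limit linear regression to the EQ-5D index, the VAS, and length of stay on a suitable scale.
4. Keep the primary composite as defined, and add a supportive analysis of the composite without frailty. Making that version the main result would redefine the primary endpoint, and it would have fewer events.
5. Label the mortality Cox model exploratory.

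The cost is a rewording of one paragraph and one extra supportive analysis. No new data, visits or patients are needed. It should be done before outcomes are analysed.
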